Given the negative feedback mechanism of homeostatic plasticity, we can propose a priming-test preconditioning TMS tool that is more effective than the current stimulation alone. Initially, subjects will receive inhibitory priming to trigger their homeostasis response, followed by an excitatory test. As a result of the preceding inhibitory treatment, the neural network near the subject’s target area will more readily generate an excitatory response, leading to a more significant neural network activity during the excitatory test compared to the excitatory stimulus alone. Homeostatic plasticity plays a critical role in maintaining neural stability; thus, its impairment could limit the efficacy of NIN interventions. Research on myasthenia gravis (18), dystonia (19–21), Parkinson’s disease (22), Alzheimer’s disease (23), depression (24) and other psychiatric disorders (25) have highlighted deficiencies in homeostatic plasticity among patients, raising concerns about its preservation in DoC patients.

Therefore, prior to administering the combined stimulation to DoC patients, it is crucial to investigate the preservation of homeostatic plasticity in these individuals. This study is guided by two hypotheses: firstly, that DoC patients exhibit impaired homeostatic plasticity, with the degree of impairment correlated with their level of consciousness; and secondly, that patients who retain homeostatic plasticity may have a more favorable prognosis. To explore the retention of homeostatic plasticity in DoC patients, this study will employ two NIN technologies, tDCS and TMS, as assessment tools.

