### Procedures

2.4

The study process will begin as early as 28 days after the patient’s injury, and the entire experimental process will be finished within 10 days. After informing the patient’s legal representative about the experimental content and potential adverse reactions, written informed consent will be obtained from them. They will be advised that they can choose to exit the study at any time without the requirement for providing a reason. After informing the healthy subjects of the experimental content and potential adverse reactions, they will sign the informed consent form.

Before the trial, DoC patients will have the option to undergo a functional magnetic resonance imaging (fMRI) scan, and they can choose to decline. Over a period of 10 days, five CRS-R assessments, and an fMRI scan will be completed. The study protocol is a repeated-measures crossover design. According to different tDCS priming protocols (anode, cathode, sham), the trial will be divided into three distinct sessions. Each session will involve 10 min of tDCS priming followed by 192 s of TMS test, with both transcranial stimulations specifically targeted toward the left M1. We will measure the motor evoked potential (MEP) amplitude at four time points: baseline (PRE), after tDCS (INTER), and at 5 and 15 min following TMS (POST-1, POST-2). CRS-R data will be collected at baseline (PRE) and 20 min after TMS (POST-3). Upon enrollment, participants will receive a serial number based on their order of enrollment, with each serial number corresponding to a randomly generated session order. Subjects will then undergo three sessions following the designated session order, with a two-day washout period between each session. The entire trial will be completed in 5 days. Patient prognostic data will be gathered at 3, 6, and 12 months after the conclusion of the study. Figure 1 provides a detailed illustration of the study flow.

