### Transcranial direct current stimulation

2.5

Homeostatic plasticity will be examined through a priming-test approach, where priming stimuli will induce and test stimuli will capture the homeostatic response (14). Previous research (28) has suggested that the fidelity of homeostatic response occurs when the prime protocol does not lead to noticeable changes in basal synaptic transmission. And prior studies (29) in mice models have demonstrated that anodal tDCS-induced LTP does not impact the efficiency of basal synaptic transmission. Therefore, tDCS is deemed the most suitable priming method, this study will also employ tDCS to trigger a homeostatic response. Given that the regulation of homeostatic plasticity involved both upward (30) and downward (31) homeostasis, anodal and cathodal tDCS were going to be used to prime upward and downward homeostasis, respectively. Sham tDCS was intended to serve as a control to evaluate the success of the priming process.

Continuous tDCS will be conducted using a DC stimulator. A steady 1 mA current will be delivered via wet sponge electrodes (7 cm × 5 cm) placed on the left M1 region and the right contralateral supraorbital area. The tDCS polarity will be determined by the electrode on the left M1. In the case of sham tDCS, only a small current pulse will occur every 550 ms (110 μA over 15 ms) instead of the actual stimulation current. The peak current will last for 3 ms, creating a brief skin sensation similar to real tDCS but lacking therapeutic benefits. To ensure the double-blind procedure, the real and sham stimulation will be managed by the code linked to the DC stimulator. Before each stimulation session, the researcher will receive the code of the session (unaware of the type of stimulation), and will start the stimulation by inputting the code to activate the DC stimulator.

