### Statistical analysis

2.11

A single transcranial stimulation typically leads to limited behavioral improvement but increases cortical excitability due to its immediate effects (36). Therefore, the primary focus of this study will be to analyze the trend of MEP changes over time in different priming types, comparing healthy individuals with DoC patients. At the individual level, the cathodal tDCS group will be compared with the sham group. The primary outcome of this study will be MEP, a measure used to assess neurophysiological changes. Since the baseline MEP in each session will be influenced by various factors such as the individual’s daily state, MEP data from different sessions will lack comparability. Therefore, all MEP data will be normalized in this study (normalized MEP = MEP/MEP baseline). The normalized MEP data will be subjected to an analysis of variance (ANOVA) to explore the retention of homeostatic plasticity in DoC patients and to determine whether the combination of cathodal tDCS and iTBS is superior to iTBS alone.

While a single stimulus may not directly lead to a change in behavior, this study will conduct a CRS-R assessment (specific item) before and after each session to ensure that any potential improvements are not overlooked. Homeostatic plasticity, as a fundamental characteristic of synapses, can impact a range of synaptic activities and may even influence levels of consciousness and prognosis. Therefore, the CRS-R score, which assesses the level of consciousness, will be considered as a secondary outcome of this study.

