Patients will be categorized into subgroups based on consciousness levels and prognosis. For consciousness levels, patients will be classified into the MCS or UWS group based on the best result from five baseline CRS-R assessments, To classify a CRS-R record as reflecting MCS, the participant must achieve at least one of the following criteria: a score of 1 on the communication subscale (intentional but non-functional yes/no communication), a score of 3 or higher on the auditory subscale (command-following), a score of 2 or higher on the visual subscale (visual fixation or better), a score of 3 or higher on the motor subscale (localization to noxious stimulation or better), or a score of 3 on the oromotor/verbal subscale (intelligible verbalization). If none of these criteria are met, the CRS-R record will be classified as reflecting UWS (37). For prognosis, patients will be evaluated at 3, 6, and 12 months, with those showing an increase of over 11 Rasch units (approximately 4–6 CRS-R points) (38) classified as the good prognosis group, while others will be placed in the poor prognosis group. A preserved homeostatic plasticity response is defined as a significant modulation of MEP amplitude following the priming-test protocol, consistent with the sliding threshold theory of synaptic plasticity. Its preservation was further compared between the MCS and UWS groups, as well as between the good and poor prognosis groups.

In this study, statistical analysis will be conducted using IBM SPSS Statistics 26 software. The collected data will first undergo normal distribution testing via Kolmogorov–Smirnov tests. If the data meets the criteria for a normal distribution, a three-way repeated measures ANOVA will then be carried out. However, if the data does not adhere to a normal distribution, Friedman’s ANOVA will be utilized instead. Following a significant outcome from the ANOVA, two-way ANOVAs will be conducted within each group to explore temporal changes in mean MEP amplitude. Additionally, Pearson correlation will be used to examine the relationship between homeostatic plasticity retention, consciousness, and prognosis. A significance level of *p* < 0.05 will be employed for determining statistical significance.

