In this study, tDCS and TMS will be used to detect homeostatic plasticity retention in patients with DoC. tDCS applies low-amplitude (1–2 mA) direct current to the brain via two scalp electrodes, modulating the threshold of action potential generation, thereby depolarizing (anode) or hyperpolarizing (cathode) individual neurons (9, 44, 45). TMS is a technique that integrates nerve stimulation and cortical excitability detection. It uses electromagnetic induction to induce secondary currents in subcortical neurons, thereby activating neurons to change physiological processes in the brain (46, 47).

While two NTBS technologies, tDCS and TMS, are widely used in the field of treatment for DoC, the selection of parameter and targets often relies on studies related to other diseases or healthy individuals. In DOC, the most common targets are the M1 or the dorsolateral prefrontal cortex (DLPFC) rather than the anterior cingulate cortex or posterior cingulate gyrus emphasized by many theories of consciousness. M1 is frequently targeted in the motor rehabilitation of stroke patients, while DLPFC is primarily employed in depression treatment (48). Such empirical transplantation carries significant theoretical risks—severe brain injury may fundamentally alter homeostatic plasticity mechanisms, and directly applying neuromodulation parameters from healthy populations may lead to diminished efficacy or even induce secondary damages such as epilepsy.

Based on these findings, we propose a stepwise intervention strategy. The primary task is to assess the retention of homeostatic plasticity in DoC patients. For patients with impaired homeostatic plasticity, priority should be given to restoring this mechanism before proceeding with neuromodulation treatments to prevent uncontrolled risks caused by impaired negative feedback regulation. Previous successes in dopamine modulation for Parkinson’s disease (22) suggest that the neurotransmitter system may serve as an important regulatory target. In some cases, impaired homeostatic plasticity might even indicate the irreversibility of a patient’s condition.

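### Preserved homeostatic plasticity is defined without checking, in the sham-tDCS session the trial already collects, that iTBS itself worked

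*Protocol article*

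**What the plan says.** Section 2.4 (Procedures) gives every participant three sessions: "According to different tDCS priming protocols (anode, cathode, sham), the trial will be divided into three distinct sessions". The test stimulus is real in all of them: "Each session will involve 10 min of tDCS priming followed by 192 s of TMS test". MEPs are taken at baseline, after tDCS, and 5 and 15 minutes after iTBS.

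Section 2.5 gives the sham session one role: "Sham tDCS was intended to serve as a control to evaluate the success of the priming process". Section 2.11 gives it a second, as comparator, since the ANOVA is also "to determine whether the combination of cathodal tDCS and iTBS is superior to iTBS alone". For individuals, section 2.11 names one comparison, cathodal against sham.

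The central construct is defined in section 2.11: "A preserved homeostatic plasticity response is defined as a significant modulation of MEP amplitude following the priming-test protocol", with the added condition that the modulation agree with the sliding threshold theory. Preservation is then compared between MCS and UWS and between good and poor prognosis, and correlated with consciousness and prognosis. Within-group two-way ANOVAs over time follow only if the overall ANOVA is significant.

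Section 2.9 plans an imaging comparison of patients with and without homeostatic plasticity. The Discussion (section 3) has one branch for impaired and one for preserved patients. For the impaired branch it puts restoration of the mechanism ahead of neuromodulation, and adds that "impaired homeostatic plasticity might even indicate the irreversibility" of a patient's condition.

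**The concern.** Homeostatic plasticity is inferred from how priming changes the response to iTBS, so absent modulation is informative only if iTBS produces a response that could have been modulated. The Introduction treats Hebbian plasticity (LTP and LTD) and homeostatic plasticity as distinct mechanisms, and the Abstract allows that severe brain injury may impair synaptic plasticity more generally. A weak or absent iTBS response in DoC is therefore foreseeable from the protocol itself. Eligibility (section 2.2) requires an obtainable MEP, not a response to iTBS.

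A patient or group in whom iTBS does nothing fails the definition of preserved for a reason unrelated to homeostasis. No wording separates that case from true loss of homeostasis.

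The first hypothesis is at stake: "that DoC patients exhibit impaired homeostatic plasticity, with the degree of impairment correlated with their level of consciousness". If iTBS responsiveness declined with severity, differences between MCS and UWS, or between prognosis groups, could appear without any difference in homeostasis.

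**Working it through.** The plan gives no figure for the iTBS response or for MEP variability, so there is no figure of its own to reproduce. The effect sizes below are assumptions. From the documents come 15 per group, 20% data loss (15 × 0.8 = 12 evaluable), one session per priming type, and 10 MEPs per time point.

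**Step 1. What each state predicts.**

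| State | Sham session, POST vs PRE | Cathodal minus sham |
|---|---|---|
| Homeostasis intact, iTBS works | facilitation | positive |
| Homeostasis lost, iTBS works | facilitation | zero |
| iTBS has no effect in any session | zero | zero |

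The last two rows agree on the priming contrast, the one named for individuals. They differ only in the sham-session time course, on which the definition does not depend.

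**Step 2. Simulation.** Assumed: n = 15, iTBS effect 0.3 on the log-MEP scale, two-sided 5% tests. Percentages are the share of runs that were significant.

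| State | SD of change | Cathodal − sham | Anodal − sham | Sham POST vs PRE |
|---|---|---|---|---|
| Homeostasis lost, iTBS works | 0.35 | 4% | 6% | 87% |
| iTBS has no effect | 0.35 | 5% | 6% | 5% |
| Homeostasis lost, iTBS works | 0.50 | 5% | 5% | 58% |
| iTBS has no effect | 0.50 | 5% | 4% | 4% |

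The priming contrasts do not separate the two states. The sham time course does, less well as variability rises.

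**Step 3. The opposite error.** With homeostasis lost, iTBS working and SD 0.35, POST vs PRE in the cathodal session alone was significant in 87% of runs. If significant modulation were read as any MEP change after priming and test, lost homeostasis could be labelled preserved. The definition needs an explicit contrast against sham.

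**Step 4. How firm a sham-session check can be.** Power of a one-sample t-test = P(|T| > t₀.₉₇₅,ₙ₋₁), where T is noncentral t with noncentrality dz × √n and dz is the mean change divided by its SD. For n = 15 and dz = 0.5, the noncentrality is 0.5 × √15 = 1.94 and the critical value 2.145, giving 44%.

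| n | dz 0.3 | dz 0.5 | dz 0.8 | dz 1.0 | dz for 80% power |
|---|---|---|---|---|---|
| 15 (one group) | 19% | 44% | 82% | 95% | 0.78 |
| 12 (after loss) | 16% | 35% | 71% | 88% | 0.89 |

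For all 30 DoC patients together, the dz detectable with 80% power is 0.53. The 95% interval half-width for the sham response at n = 15 and SD 0.35 is 2.145 × 0.35 / √15 = 0.19 log units, against an assumed effect of 0.3. At SD 0.50 it is 2.145 × 0.50 / √15 = 0.28. A non-significant sham test therefore cannot prove that iTBS had no effect.

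**The case against.** The strongest reply is that the design already contains the answer. Sham tDCS plus iTBS is an iTBS-alone arm within each participant, section 2.11 uses it as such, and the primary focus is the MEP time course by priming type in healthy and DoC participants. This stands. A reader might infer that the trial cannot tell failed homeostasis from failed iTBS, or that sham serves only as a priming check. The documents support neither. The gap lies in the definition and the interpretation.

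Second, only *preserved* is defined, with a condition tied to the sliding threshold theory, and a patient-level rule may be left to an analysis plan. This stands in part: that everything else is impaired is an inference. But the sliding-threshold condition narrows what counts as preserved, so a flat responder still fails it, and sections 2.9 and 3 use only two categories.

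Third, the MEP exclusion, iTBS intensity set from the individual motor threshold, and the T1 check of M1 make it less likely that the stimulus misses its target. True, but none of these shows that iTBS changes excitability.

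Fourth, a reader might expect a flat DoC response to be the likeliest finding under the sponsor's hypothesis. It is not: lost negative feedback with working iTBS predicts similar facilitation whatever the priming. Nor must priming contrasts vanish whenever sham-primed iTBS shows nothing, since cathodal priming could lower the LTP threshold enough to reveal a response. The Discussion's consequences are also hedged and are not trial decision rules.

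**Conclusion.** The point holds as one about definition and interpretation. As written, absent modulation by priming is read the same way whether homeostasis is lost or iTBS is ineffective, although the session that would distinguish them is collected. Under the assumed effects the priming contrasts are significant in about 4% to 6% of runs in both states, while the sham-session change is significant in 58% to 87% against 4% to 5%.

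How often DoC patients would be mislabelled cannot be computed, because the protocol gives neither an iTBS response rate nor MEP variability. A reader might scale the priming effect in proportion to the iTBS response and derive a specific degree of false impairment. That rests on a multiplicative model the documents do not contain.

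The check has limits. It is imprecise at 15 per group and weaker still for one patient. With no session without iTBS, drift over time within the sham session would be counted as iTBS response.

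**What to change.** 1. Define preservation as a priming-by-time contrast against the sham session, in the direction the sliding threshold theory predicts (larger response after cathodal priming, smaller after anodal), not as any significant MEP change after priming and test.
2. Report the sham-session iTBS response (POST vs PRE) with its confidence interval in healthy controls, MCS and UWS beside the priming contrasts, whether or not the overall ANOVA is significant. Because normalised baseline equals 1 for everyone, test the log ratio against zero.
3. Conclude impaired homeostatic plasticity for a group only if its sham session shows an iTBS response and its priming contrast is smaller than in healthy controls. Where neither the sham session nor priming shows a response, conclude *not assessable*. Do not treat a non-significant sham test alone as proof of no response.
4. Allow the same third category for patients, and treat individual labels as exploratory.
5. Show the MCS/UWS and prognosis comparisons for the sham-session response beside those for the priming contrast. Do not adjust the cathodal-minus-sham contrast for the sham response, which is part of that contrast and would build in mathematical coupling.

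The cost is wording in the protocol and analysis plan, with no new data or visits. Some patients or groups will become not assessable, and the impairment claim will be more cautious.

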### Sample size

2.3

The sample size calculations had been performed using G*power 3.1 (26) with prior power analysis. Based on previous studies of DoC patients (27), the effect size f had been calculated to be 0.3. A three-way repeated measures ANOVA had been conducted with test power (1-*β*) set at 80% and the type I error rate (*α*) of 5%. Taking into account an allocation ratio of 1:1:1 and a 20% data loss rate, this had resulted in a minimum of 15 participants per group.

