### Cortical excitability measurements

2.7

This study will evaluate the cortical excitability of the motor cortex at four time points: BASELINE, INTER, POST1, and POST2, to investigate if priming stimuli induce and test stimuli capture the homeostatic response. Single-pulse TMS will be utilized to stimulate the motor cortex and generate MEPs in the peripheral muscles. The amplitude of these MEPs will indicate motor cortical excitability. We will administer 10 single-pulse TMS (stimulation intensity: 120%RMT; time interval: 5 s) to target the left M1 at four time points. Motor cortex excitability will be represented by averaging the peak-to-peak amplitudes of MEPs induced on the FDI muscle of the right hand, recorded during the experiment. The FDI muscle will be chosen for its small, localized, and palpable nature (34). MEPs will be recorded using the Ag-AgCl surface electrode provided with the TMS device. The EMG signal will undergo filtering and digitization using an analog–digital converter, then will be processed with low-pass, high-pass, and 50 Hz-Notch-Filter before being storage in a personal computer for offline analysis.

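### The planned repeated-measures ANOVA classically keeps only participants with all 12 MEP blocks, so one lost block or session discards the rest; a mixed model would keep it

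*Protocol article*

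**What the plan says.** All places are in the protocol article.

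- **Procedures (2.4), sessions:** "According to different tDCS priming protocols (anode, cathode, sham), the trial will be divided into three distinct sessions".
- **Procedures (2.4), measurements:** "We will measure the motor evoked potential (MEP) amplitude at four time points", namely baseline, after tDCS, and twice after iTBS.
- **Cortical excitability measurements (2.7):** at each time point, "We will administer 10 single-pulse TMS", and the amplitudes are averaged. One block is thus a mean of ten responses.
- **Statistical analysis (2.11), outcome:** MEP is the primary outcome, analysed after within-session scaling, "normalized MEP = MEP/MEP baseline".
- **Statistical analysis (2.11), method:** after a normality test, "a three-way repeated measures ANOVA will then be carried out"; otherwise, "if the data does not adhere to a normal distribution, Friedman’s ANOVA will be utilized instead". On software, "statistical analysis will be conducted using IBM SPSS Statistics 26 software".
- **Sample size (2.3):** "Taking into account an allocation ratio of 1:1:1 and a 20% data loss rate", the minimum is 15 participants per group.

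The article does not say which SPSS procedure will be used, what happens when a block is missing, or how often blocks are expected to fail.

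**The concern.** The issue is the method that the plan does name, not the lack of a missing-data section. Classical repeated-measures ANOVA works on one complete row per participant, and so does Friedman's test. Neither branch of the stated plan makes use of a partly complete participant.

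The design makes incomplete rows foreseeable. Measurements are spread over three separate sessions, participants may leave at any time, and the sample size itself expects data loss. The normalization adds a further route: a failed baseline block leaves all three later values of that session undefined.

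What is at stake is usable data in a small trial. Someone with complete cathodal and sham sessions but a missing anodal session would contribute nothing to the three-way analysis. Yet one stated aim of the ANOVA is to show whether cathodal priming plus iTBS beats iTBS alone, and that participant carries full information on it.

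**Working it through.** **Inputs from the protocol article.** 3 sessions and 4 time points (2.4); 15 per group in 3 groups, f = 0.3, power 80%, alpha 5%, 20% loss (2.3); division by the session baseline (2.11).

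**Step 1: the plan's own figure.** 15 × (1 − 0.20) = 12 evaluable per group, or 36 of 45. The article gives neither the number of repeated measures nor their correlation, so 15 cannot be reproduced uniquely. With noncentrality f²·N·m/(1 − ρ) for the group-by-within interaction in three groups:

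| m (assumed) | ρ (assumed) | Total N for 80% power | Per group | After 20% loss, rounded up |
|---|---|---|---|---|
| 3 | 0.3 | 36 | 12 | 15 |
| 3 | 0.5 | 27 | 9 | 12 |
| 4 | 0.5 | 24 | 8 | 10 |

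The figure of 15 is attainable and is not shown to be wrong.

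**Step 2: blocks needed.** 3 × 4 = 12 per participant and 45 × 12 = 540 in the trial. Only 9 normalized values per participant are post-baseline, but the 3 baselines are needed to form them.

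**Step 3: a count that needs no probability model.** The allowance covers 45 × 0.20 = 9 participants. Nine lost blocks in nine different participants, 9/540 = 1.7% of blocks, would leave nine incomplete rows.

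**Step 4: independent losses (assumed).** If each block is lost with probability p, the chance that a participant is incomplete is 1 − (1 − p)^12.

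| p | Incomplete | Expected complete of 45 | Expected complete of 15 | Chance that at least 12 of 15 are complete |
|---|---|---|---|---|
| 1% | 11.4% | 39.9 | 13.3 | 92% |
| 2% | 21.5% | 35.3 | 11.8 | 59% |
| 3% | 30.6% | 31.2 | 10.4 | 28% |
| 5% | 46.0% | 24.3 | 8.1 | 4% |

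Setting the incomplete share to 20% gives p = 1 − 0.80^(1/12) = 1.84%.

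**Step 5: clustered losses (assumed).** Blocks in one participant share the hotspot, the motor threshold and the patient's state, so failures would plausibly come together. The share of lost blocks that makes 20% of participants incomplete is then:

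| Loss pattern | Share of blocks lost |
|---|---|
| Clustered by participant (beta-binomial), intraclass correlation 0.1 | 2.8% |
| Same, 0.3 | 4.7% |
| Same, 0.5 | 7.1% |
| Whole sessions lost independently, 1 − 0.80^(1/3) | 7.2% |
| Whole participants lost | 20% |

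**Step 6: what a mixed model recovers.** It keeps every remaining normalized value of a participant with a missing post-baseline block, and the other two sessions of a participant with a missing session. If the baseline block fails, that session is still lost, because its ratios cannot be formed, but the other two stay. If the whole participant is lost, nothing is recovered.

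**The case against.** The strongest objection is that this is a missing-data policy in disguise. The article names an ANOVA and a software package; it does not say that incomplete participants are dropped, and a rule for repeating or imputing a failed block may stand in an analysis plan that is not shown. That is right as far as it goes: deletion is a property of the named methods as usually run, not a written rule. But the named methods are themselves the choice under review. An analysis plan that followed them would inherit the problem unless it added such a rule.

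Second, nothing in the documents supports any particular loss rate. A block averages ten pulses, so it is missing only if the whole block fails. Patients without an MEP in the right first dorsal interosseous muscle, or with unstable vital signs, are excluded. Withdrawal removes remaining sessions or whole participants rather than isolated blocks. All of this stands, which is why the figures are a range.

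Three stronger readings are tempting and not supported:

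- *About 2% missing blocks will exhaust the allowance.* This holds only under independent losses, the low end of the range.
- *The trial would be underpowered.* At 2% independent loss the expected number complete is 35.3 against an implied 36, and Step 1 shows that fewer than 12 per group can suffice under other assumed correlations.
- *Dropping incomplete participants biases the comparison of DoC patients with healthy controls.* The documents give no loss rates by group and no link between loss and MEP response. If loss depended on unobserved values, a mixed model would not remove the bias either.

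Finally, the individual-level comparison of cathodal with sham (2.11) does not inherently need the anodal session, so the loss described here concerns the three-way analysis.

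**Conclusion.** The point holds in conditional form. The stated analysis and its fallback classically use only participants with all 12 blocks, and so discard usable sessions in a trial that plans for data loss. How much is discarded cannot be settled from the documents. The 20% allowance would be used up at about 1.8% of blocks if losses are independent, about 3% to 7% if they cluster by session or patient, and 20% if whole participants are lost.

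This rests on two assumptions: that the usual complete-case form of the ANOVA is meant, and that no rule elsewhere replaces failed blocks. No bias and no definite shortfall of power is claimed. The change is worth making because it is cheap and the implied evaluable number, 12 per group, leaves little to waste.

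**What to change.** In Statistical analysis (2.11), make the primary analysis a linear mixed model, fitted in the same software to all available post-baseline normalized MEP values:

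- fixed effects for group, priming, time, all their interactions, and session order;
- random intercepts for participant and for session within participant;
- small-sample degrees of freedom, given about 15 per group.

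If residuals are clearly non-normal, fit the same model to log-transformed ratios instead of switching to Friedman's ANOVA, which would bring back the complete-row requirement. Keep the complete-case three-way ANOVA as a sensitivity analysis. State that a session without a usable baseline block is excluded while the participant's other sessions are kept.

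The cost is a change of wording and slightly more analysis work, with no extra participants, visits or measurements. The model relies on data being missing at random, and the text should say so.
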